### Phases of the study

2.2

The study will be divided into 3 main phases, as shown in Figure 1:

Phase 1: Baseline assessment of female teachers of public secondary schools.Phase 2: Intervention adaptation and implementation in female teachers of public secondary schools.Phase 3: End-line assessment in female teachers of public secondary schools.

**Figure 1 fig1:**
[figure not shown]
Phases of the Study: this figure outlines the three main phases of our research, including a baseline phase, followed by intervention development and finally an endline assessment.

#### Phase 1: baseline assessment of outcome variables of the study participants

2.2.1

The baseline assessment of the following variables will be conducted:

Behavior and knowledge assessment—these will include questions on dietary intake, physical activity, awareness on lifestyle risk factors of NCDs. These were included in the study as 40% of all cancers and 80% of heart diseases can be attributed to behavioral risk factors, four of which are most prevalent; smoking, alcohol consumption, physical inactivity and unhealthy diet. However, there remains a lack of surveillance and reporting of these risk factors at local, national and international levels. If recognized and managed early, the NCD burden and severity could be reduced by a great extent (35). The modern day strategy to manage NCDs is based on the risk factor management of these diseases, particularly the modifiable or behavioral risk factors. It involves making changes at individual, societal, national, and international levels by increasing awareness regarding the behaviors leading to NCD development and developing policies to control the occurrence of these risk factors among communities, such as tobacco control laws, regulation of sugar sweetened beverages, development of physical activity opportunities at work and educational institutes (36). Our study aims to include the mentioned behavioral risk factors and determine the impact a lifestyle modification intervention can have in reducing them. This can have policy implications, as in case of favorable results the proposed lifestyle modification can be implemented at the local or regional levels.Anthropometric or physical measurements—We have included body mass index (BMI), waist circumference (WC), hip circumferences (HC), waist to hip ratio (WHR), and waist to height ratio (WhTR) in our study to determine obesity risk and levels in the study population. Obesity is a vital risk factor for non-communicable diseases and contributes to metabolic disturbances seen in various NCDs. Over the years, body mass index (BMI) has been used to determine the level of obesity in individuals, but recently other anthropometric measurements have been considered to classify obesity. These include waist circumference (WC), hip circumferences (HC), waist to hip ratio (WHR), and waist to height ratio (WhTR). All these measurements either independently or coupled with BMI have been seen to accurately estimate abdominal obesity and visceral fat, both of which are risk factors for NCDs. Studies have concluded BMI, WC and WHtR as reliable anthropometric estimates of obesity which can then be used to accurately detect obesity and subsequent NCDs, particularly in women as abdominal fat is associated with greater risk of developing NCDs in the female population (37). An Indian study aimed to assess the association between anthropometric measurements and NCD risk and found that in adults aged more than 45 years, are 61 and 98% more likely to develop NCDs and multi-morbidities if they have high waist to hip (WHR) and high waist circumference (WC), respectively (38). Therefore, employing anthropometric measurements as an assessment factor for NCDs can help provide a clear picture of the level of NCD development risk in the population.

#### Phase 2: intervention development and implementation

2.2.2

The intervention phase will involve exposing the intervention group to nutrition and physical activity knowledge in the form of educational sessions, which will be divided into 12 sessions. Three sessions will be given each month for the first 6 months, and two sessions will be given each month for the last 3 months. The intervention sessions will be delivered by trained health professionals including registered dietitians, and physical fitness experts. The intervention will be delivered in a group format where the participants will receive joint counseling. However, participants will be encouraged to seek individualized guidance during or after sessions, to address any personal concerns. Individualized diet plans may also be administered to participants with special needs or multiple risk factors. This will ensure tailored support within a group-based framework.

Nutrition intervention—will comprise of bimonthly education and counseling sessions on healthy food choices, identifying and reducing intakes of unhealthy foods, equipping participants to prepare healthy meals from the foods available at home, self-monitoring of eating habits and NCD risk factors, and incorporating nutrition guidelines from Pakistan Dietary Guidelines for Better Nutrition (PDGN) into daily life. A total of 12 sessions will cover important nutrition topics to increase participant awareness of healthy diets and individual diet plan provision will help them guide them in their daily nutrient intake. The topics for these sessions are given below:Physical activity intervention—will include physical activity education and training sessions as per the Pakistan Dietary Guidelines for Better Nutrition (PDGN) recommendations, and WHO physical activity guidelines. One session per 15 days will be done and participants will be guided on how to incorporate physical activity in their daily routine. Aerobic exercises such as walking and jogging will be promoted and the use of pedometers will be encouraged to count daily steps. Each participant will be advised to walk at least 30 min every day for a minimum of 5 days a week as per WHO guidelines.

The topics for these sessions are given in Figures 2, 3.

**Figure 2 fig2:**
[figure not shown]
Nutrition intervention session topics: this figure covers the weekly nutrition education sessions tailored to female secondary school teachers, as part of the proposed intervention to reduce NCDs risk.

**Figure 3 fig3:**
[figure not shown]
Physical activity intervention session topics: this figure includes topics relevant to physical activity promotion in female teachers and reducing barriers to physical activity as part of a tailored lifestyle education intervention.

Nutrition interventions will be designed in direct alignment of the Pakistan Dietary Guidelines for Better Nutrition (PDGN). These guidelines are specifically designed to meet the nutritional needs and dietary patterns of the Pakistani population. Nutrition sessions will be tailored according to the following key PDGN sections:

Nutritional status of adults (19–60 years)Relationship between diet and diseaseTraditional and fast foodsSalt consumptionGlycemic index of foodsNutrition labelingOverweight and obesityPhysical activity and lifestyle behaviorPakistan dietary guidelines for better nutritionFood and serving size for adults (19–60 years)Sample menu for adults (19–60 years)Dietary Messages

The physical activity sessions will include recommendations from the PDGN’s Annexure-XIII: Recommendations on physical activity for different age groups, which have been developed considering the Pakistani population’s contextual factors. Furthermore, the WHO’s physical activity guidelines will also be used as a reference to shape the intervention according to the study population, in order to ensure the global physical activity standards for NCD prevention. Additionally, thrice weekly group exercise sessions will be arranged to promote physical activity guidelines adherence.

Intervention fidelity will be ensured through content validation of the session material through subject experts who will ensure the intervention is relevant to study objectives. Additionally, a session plan will be developed and adhered to, to ensure all material is delivered timely and accurately. Standardized checklists and attendance logs will be maintained for each session to assess content delivery and participant engagement. Furthermore, study participant adherence will be ensured through weekly text message check-ins in participant WhatsApp groups. Secondly, participants will be asked to maintain bi-monthly dietary logs or diaries. Moreover, sessions will be scheduled according to teachers’ availability in consultation with school administration to promote their participation.

The control group will go about their usual routine and will receive no nutrition or physical activity related sessions or educational material during the study period. Once the study has concluded they will be given lifestyle intervention sessions as an ethical consideration. However, to ensure consistency in data collection and monitoring, the control group will undergo standardized follow-up assessments at the same time frames as the intervention group (baseline and endline). Additionally, monitoring visits will be conducted at the control group schools to ensure engagement, minimize attrition, and warrant consistent study conditions. Lastly, fidelity checks will be conducted during data collection, by research supervisors, to ensure standardized administration of questionnaires and anthropometric measurements.

#### Phase 3: end-line assessment of outcome variables

2.2.3

Evaluation phase to assess the impact of the intervention in each group as well as to compare the impacts of the interventions with each other. This phase will also include in-depth interviews of participants to identify the facilitators and barriers that played a role in either helping them follow the dietary guidelines given or not be able to do so. Additionally, the reasons behind their knowledge, attitudes and practices regarding NCDs and their risk factors will be explored via focus group discussions.

### Study area

2.3

The study area will be Islamabad city, and schools from the city will be included. The reason for choosing Islamabad city is because the prevalence of non-communicable diseases is higher in the urban areas as compared to the rural areas of Pakistan as reported by the Pakistan Demographic and Health Survey 2017–18. The survey found a direct association between education and wealth status and non-communicable disease and risk factor prevalence, with 40% women with the highest wealth status being overweight as compared to 16% women of low socio-economic status. Among the provinces and cities, Islamabad reported the highest prevalence of overweight and obese women (68%). Therefore, female educators in Islamabad form a vulnerable group in terms of NCD development and an intervention targeting these women can help reduce their risk of developing these diseases later in life.

### Duration of study

2.4

The study will be conducted over a period of 17 months and the timeline will be as follows:

Phase 1 - Baseline data collection – 02 months.

Phase 2 - Intervention development and implementation

Phase 2a - Planning and adaptation of interventions − 02 monthPhase 2b - Pre-testing the intervention − 02 monthsPhase 2c - Intervention implementation − 09 months

Phase 3 - Evaluation of intervention impact − 02 month.

### Data sources

2.5

This study will involve primary data collection and employ the questionnaire method of gathering data from participants. Participants who have given their consent to be a part of the study will be asked to fill in the adapted and validated questionnaires containing different variables of interest.

### Study population

2.6

The study population will be all female teachers employed in the public secondary schools of Islamabad.

### Sampling technique

2.7

Study will be a 2 stage cluster sampling, as the sampling procedure will be divided into 2 steps.

#### Stage 1: selecting schools

2.7.1

Defining clusters: all public schools within Islamabad city will be considered clusters.Sampling frame: list of all public schools in Islamabad city will be the sampling frame and will be obtained from the education department.Number of schools selected: according to Pakistan Education Statistics report (2021–22) 15 teachers on average in each school – 130/15 = 8 schools selected via purposive sampling. Purposive sampling was chosen to select schools based on practical considerations such as administrative permissions and accessibility, institutional cooperation, and the practicality of implementing a lifestyle intervention in real-world school settings. This will enhance the study’s contextual relevance, and help understand the feasibility of future up-scaling within similar environments (39). Employing purposive sampling may limit the study’s applicability to other population groups such as private or rural school teachers. However, utilizing purposive sampling will help prioritize contextual comprehension and intervention feasibility at a deeper level. This is consistent with implementation research frameworks that prioritize situational understanding over statistical representativeness (40).

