#### Stage 2: selecting teachers within schools

2.7.2

Sampling frame: list of teachers from each selected school will be obtained from the school’s administration and will serve as a sampling frame.Selection of participants – all female school teachers will be screened for NCD risk factors using the WHO STEP wise Approach to NCD Risk Factor Surveillance (STEPS) tool, which includes both behavioral assessment (Step 1) and anthropometric measurements (Step 2). Teachers identified in the screening process to meet predefined NCD risk criteria, will be considered eligible for the study and will be selected via simple random sampling such as lottery method to be enrolled in either intervention or control arm.

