### Sample size calculation

2.8

The sample size is calculated on the basis of BMI reported from a similar study conducted in India (41) using the formula: $n=[2\times (\sigma^{2})\times {\left(Z₁-\alpha /₂+Z₁-\beta \right)}^{2}]/d^{2}$

Where SD = 0.96.

Alpha = 0.05.

Power of study = 80%.

Effect size = 0.5.

Non-response rate = 10%.

Sample size = 65 per group and total sample = 130 teachers (both groups).

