### Sample recruitment: inclusion and exclusion criteria

2.9

Inclusion and exclusion criteria for the study is shown in Table 1. Female teachers of selected public secondary schools meeting the inclusion criteria will be approached and those consenting to be a part of the study will be recruited.

**Table 1 tab1:** Inclusion and exclusion criteria.

Inclusion criteria	Exclusion criteria
Females aged 30 to 45 years of age.	Female teachers who are undergoing any medicinal, herbal, or nutritional therapies.
Females who have not been medically diagnosed with a non-communicable disease.	Pregnant and breastfeeding females.
Females who have one or more of the non-communicable disease risk factors: BMI > 25 kg/m^2^ Waist circumference > 88 cm Fruit and vegetable intake < 5 servings per day Physical activity < 150 min/week	Female teachers who will not be staying in the school for the next 9 months

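### The school count of eight rounds 130/15 down: at the stated average, eight schools hold 120 teachers, so the sample of 130 is not supported by the plan's own figures

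*Protocol article*

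**What the plan says.** Section 2.7.1 takes from a national education report that there are "15 teachers on average in each school" and derives the school count directly from it: "130/15 = 8 schools selected via purposive sampling". The stated grounds for choosing schools are permissions, accessibility, cooperation and practicality. School size is not among them.

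Section 2.8 sets the target: "Sample size = 65 per group and total sample = 130 teachers (both groups". It uses an SD of 0.96, a two-sided alpha of 0.05, a non-response rate of 10%, and the entries "Effect size = 0.5" and "Power of study = 80" (per cent).

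Not every teacher in a chosen school can take part. Table 1 in section 2.9 requires, among other things, "Females aged 30 to 45 years of age" and "Females who have not been medically diagnosed with a non-communicable disease". It excludes women on medicinal, herbal or nutritional therapy, those who are pregnant or breastfeeding, and those who will leave the school within 9 months. Consent is also needed. Under section 2.7.2, teachers who meet the risk criteria on screening "will be considered eligible for the study and will be selected via simple random sampling".

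**The concern.** The division has two faults. The quotient is rounded down, although the question is how many schools are needed to supply 130 teachers. It also treats every teacher as a participant, although sections 2.7.2 and 2.9 screen the staff and then ask for consent.

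The school count is settled early and depends on permissions. If a shortfall shows only after screening, the options left are to enrol fewer teachers, loosen eligibility or bring in schools late. The article announces none of these. Each would cost something in a non-randomised difference-in-differences design with a single pre-intervention time point, where the comparison leans on baseline similarity of the two groups.

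**Working it through.** **Inputs.** Required total 130, i.e. 65 per group (section 2.8). Average of 15 teachers per school and 8 schools (section 2.7.1). SD 0.96, difference d = 0.5, two-sided alpha 0.05, power 80%, non-response 10% (section 2.8). The eligible-and-consenting fraction f is not given, so it is an assumption here, shown at 100%, 80% and 60%.

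**Step 1: reproduce the plan's sample size.** n = 2 × SD² × (z₁₋α/₂ + z₁₋β)² / d² = 2 × 0.9216 × (1.960 + 0.842)² / 0.25 = 57.87, so 58 per group (116 in all). Allowing for 10%: 58 / 0.9 = 64.4, so 65 per group and 130 in total. The plan's figure reproduces.

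**Step 2: the school count.** 130 / 15 = 8.67, which rounds up to 9. The stated 8 appears only by rounding down. 8 × 15 = 120, which is 10 (7.7%) below 130; 9 × 15 = 135. To supply 130, eight schools would need 130 / 8 = 16.25 enrolled teachers each on average.

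**Step 3: does the 10% allowance cover the gap?** 120 × 0.9 = 108, below the 116 that the formula needs. For eight average schools to deliver 116 analysed, 116 / 120 = 96.7% of all their teachers would have to be eligible, consent and complete.

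**Step 4: power under the plan's own formula.** With m analysed per group, power = Φ(d / (SD × √(2/m)) − 1.960). For m = 54: 0.5 / (0.96 × √(2/54)) = 2.706, and Φ(0.746) = 77.2%.

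| f (assumed) | Teachers from 8 schools | Power, all analysed | Power after 10% loss | Schools for 130, from 130/(15f) | Rounded up to an even number |
|---|---|---|---|---|---|
| 100% | 120 | 81% | 77% (108 analysed) | 9 | 10 |
| 80% | 96 | 72% | 68% (86.4) | 11 | 12 |
| 60% | 72 | 60% | 55% (64.8) | 15 | 16 |

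Both power columns are shown because section 2.8 calls the 10% non-response. If that already means refusal, and f also includes consent, removing a further 10% counts refusal twice and the all-analysed column applies. The formula treats teachers as independent; none of these figures allows for clustering by school.

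**The case against.** The strongest reply is that 15 is a national average and does not cap the schools that will be chosen. Selection is purposive, so the team could pick larger schools, and eight averaging 16.25 enrolled teachers would reach 130. This stands. A reader might infer that the sample cannot be reached, and the documents do not support that. They support only that it does not follow from the stated inputs, since no size criterion is given.

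Second, the part of the shortfall that rests on the documents alone is small. The 120 teachers exceed the 116 analysed that the formula needs, and if all are analysed power is about 81%. This also stands. The lower powers depend on assumed fractions.

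Third, an article may leave the expected eligible share to the full protocol. That is fair, and its absence is not the fault raised here. The fault is a printed quotient that is wrong and that equates teachers employed with teachers enrolled.

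Two further inferences are tempting. One is that the lottery in section 2.7.2 would have nobody to leave out. The same sentence continues with enrolment into either arm, so the lottery may serve as allocation and would keep that function in a small pool. The other is that more schools would lower the design effect. At a given f each school yields 15f teachers whether 8 or 15 schools take part, so the cluster size is no smaller than eight schools would actually give.

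**Conclusion.** The point holds as an error in a stated planning figure. On the article's own numbers eight schools supply 120 teachers, 10 short of 130, before eligibility and consent are considered. The size that rests on the documents alone is about 77% power against the planned 80% if all 120 enrol and 10% are lost, and no loss of power if nobody is lost. Larger losses are plausible, because the Table 1 criteria and consent apply to whole school staffs, but their extent is unknown. The figures of 72% and 60% (68% and 55% after a further 10% loss) are conditional on assumed fractions of 80% and 60%. The target of 130 itself reproduces and is not in question, and nothing here touches the planned analysis.

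**What to change.** In section 2.7.1, replace the quotient by 130 / (15 × f), rounded up. State f as an assumption drawn from the schools' teacher lists or from screening. Even with f = 100% this gives at least 9 schools, or 10 if the arms are to have equal numbers of schools. Alternatively, keep eight schools and add a minimum size to the selection criteria, so that they can be expected to average at least 16.25 eligible, consenting teachers. If only eight schools of average size are feasible, state the sample they are expected to yield and its power.

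Extra schools cost more than permissions: section 2.2.2 also provides for education sessions, thrice-weekly group exercise and monitoring visits at control schools. A minimum size narrows the choice of schools. Restating the expected sample and power is a change of wording only, at the price of admitting lower power.

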#### Stage 2: selecting teachers within schools

2.7.2

Sampling frame: list of teachers from each selected school will be obtained from the school’s administration and will serve as a sampling frame.Selection of participants – all female school teachers will be screened for NCD risk factors using the WHO STEP wise Approach to NCD Risk Factor Surveillance (STEPS) tool, which includes both behavioral assessment (Step 1) and anthropometric measurements (Step 2). Teachers identified in the screening process to meet predefined NCD risk criteria, will be considered eligible for the study and will be selected via simple random sampling such as lottery method to be enrolled in either intervention or control arm.

### Sample size calculation

2.8

The sample size is calculated on the basis of BMI reported from a similar study conducted in India (41) using the formula: $n=[2\times (\sigma^{2})\times {\left(Z₁-\alpha /₂+Z₁-\beta \right)}^{2}]/d^{2}$

Where SD = 0.96.

Alpha = 0.05.

Power of study = 80%.

Effect size = 0.5.

Non-response rate = 10%.

Sample size = 65 per group and total sample = 130 teachers (both groups).

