Recently, a large body of evidence has depicted positive results of lifestyle modification on reducing non-communicable diseases risk factors in both men and women. Physical activity and improved diet have a significant impact on reducing weight, decreasing overall fat intake and increased fiber intake, all of which help reduce lifestyle risk factors (15). Pairing preventive cardiovascular disease screening with lifestyle interventions focused on dietary and physical activity modifications produced small but long-term health benefits in women, especially those with preeclampsia (16). Whether diet or physical activity or both produce the greatest impact on reducing non-communicable disease risk factors depends on a number of factors such as the type of diet, intensity and duration of physical activity and other physiological conditions such as pregnancy, post-partum or lactation (17). Lifestyle interventions including both nutrition and physical activity components can produce modest health impacts in as little as 6 weeks. Improvements were seen in the body mass index (BMI), arm, chest, waist and hip circumferences, body far percentage, and blood glucose levels after a one and a half month aerobic training and nutrition education community program targeted toward women aged 50 years and above (18).

Teachers working at primary and secondary schools depict similar lifestyle behaviors and have below par health status. About 80.9% of female school teachers lacked adequate nutrition knowledge, and 17.6% were obese (19). Evidence has shown that improving the lifestyle related knowledge and behaviors in teachers can directly and positively impact the nutritional and physical activity associated behaviors in students (20). Additionally, studies have found teachers to have a higher prevalence of unhealthy lifestyles and overall a poorer health status, as compared to medical professionals or entrepreneurs (21). Furthermore, poor health in teachers then leads to increased absenteeism and even early retirement as the quality of life further deteriorates. Evidence has depicted a positive impact of physical activity interventions on reducing stress, and employee turnover, while improving health outcomes. This ultimately increases the overall education system productivity and reduces healthcare costs (22).

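### The 80% power figure makes no allowance for clustering although schools are defined as clusters, and its SD of 0.96 and effect of 0.5 are unlabelled

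*Protocol article*

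**What the plan says.** Section 2.8 names the basis of the calculation: "The sample size is calculated on the basis of BMI reported from a similar study conducted in India (41". It gives the standard formula for comparing two independent means, with SD 0.96, two-sided alpha 0.05, "Power of study = 80"%, "Effect size = 0.5" and "Non-response rate = 10"%. The result is "Sample size = 65 per group and total sample = 130 teachers (both groups").

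The design sections describe something else:

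- Section 2.7 calls the sampling two-stage cluster sampling. Section 2.7.1 says "all public schools within Islamabad city will be considered clusters" and selects 8 schools at about 15 teachers each.
- Section 2.2.2 delivers the sessions in a group format with joint counselling. The paragraph on the control group there speaks of monitoring visits to control schools, which implies that whole schools form the arms.
- Section 2.7.2 has eligible teachers drawn by lottery into either arm, which implies individual allocation.
- Section 2.1 makes the effect estimate a difference-in-differences, that is, a comparison of changes.

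No ICC or design effect appears in the article.

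**The concern.** Teachers in the same school, or in the same session group, tend to resemble each other in how their BMI changes. A formula that treats them as independent understates the standard error, and the power it reports is too high unless the ICC is negligible.

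The power figure also depends on what the SD describes. An SD of 0.96 would be very small for BMI across women, but it could describe change within women. The article says only BMI.

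BMI is a primary outcome in section 2.12.1, and the conclusion expects the findings to inform policy and scale-up. A null result read against a stated 80% power would be taken as fair evidence of no useful effect, although the design may have offered considerably less.

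**Working it through.** **1. Reproduce the stated figure.** Inputs from section 2.8: SD 0.96, difference 0.5, (1.960 + 0.842)² = 7.849.

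n = 2 × 0.96² × 7.849 / 0.5² = 57.9, so 58 per group; 58 / 0.90 = 64.4, so 65.

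The figure reproduces exactly, and nothing is left over that could be a design effect.

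**2. What 0.5 must be.** As a standardized effect (SD 1), n = 2 × 7.849 / 0.25 = 62.8, so 63; 63 / 0.90 = 70. That does not give 65. So 0.5 is a raw difference in the units of the SD, presumably kg/m², despite its label.

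**3. Power if whole schools form the arms.** Analysed: 58 per arm, 116 in 8 schools, so m = 116 / 8 = 14.5. Design effect DE = 1 + 13.5 × ICC; SE = 0.96 × √(2 × DE / 58). With 8 schools in two arms, a school-level test has 8 − 2 = 6 degrees of freedom. The ICCs are assumptions.

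| ICC | DE | SE | Power, normal | Power, t on 6 df | Detectable at 80%, 6 df |
|---|---|---|---|---|---|
| 0 | 1.00 | 0.178 | 80% | 65% | 0.60 |
| 0.01 | 1.14 | 0.190 | 75% | 60% | 0.64 |
| 0.02 | 1.27 | 0.201 | 70% | 55% | 0.68 |
| 0.05 | 1.68 | 0.231 | 58% | 44% | 0.78 |
| 0.10 | 2.35 | 0.273 | 45% | 34% | 0.92 |

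The row for ICC 0 separates two effects. Having only 8 schools takes power from 80% to 65% before any correlation enters; the ICC takes the rest. On the normal approximation, an ICC of 0.004 already lowers power to 78%.

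**4. Power if teachers are allotted individually.** Each school then contributes to both arms and its stable level largely cancels. Clustering remains mainly in the intervention arm, through shared sessions. SE = 0.96 × √((DE + 1) / 58), with DE applied to that arm only. Session-group size is not stated; about 7 to 15 is assumed.

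| ICC | DE, groups of 7 to 15 | Power, normal |
|---|---|---|
| 0.01 | 1.06 to 1.14 | 79% to 77% |
| 0.05 | 1.30 to 1.70 | 74% to 68% |
| 0.10 | 1.60 to 2.40 | 69% to 58% |

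The 6 degrees of freedom do not apply here.

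**5. What 0.96 can be.** Section 2.3 states "Islamabad reported the highest prevalence of overweight and obese women (68"%); the Introduction reports of female teachers in a cited study that "17.6% were obese". Assume normality, cut-offs of 25 and 30 kg/m², and that the two sources may be combined.

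- If 0.96 were the SD across women with 68% above 25, the mean would be 25 + 0.468 × 0.96 = 25.4, and about one woman in a million would exceed 30.
- The two percentages together imply SD = (30 − 25) / (0.468 + 0.931) = 3.6. With cut-offs 23 and 27.5 it is 4.5 / 1.398 = 3.2.
- For an SD of change of 0.96, the correlation between baseline and end-line must be 1 − 0.96² / (2 × SD²): 0.96 at either SD.

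**The case against.** The arithmetic of section 2.8 is correct; the dispute is about design assumptions and labels. Four points on the other side carry weight.

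- **Allocation.** The larger losses apply only if whole schools form the arms. Section 2.7.2 can be read as an individual lottery, and the loss is then much smaller. This stands, and is why both cases are shown.
- **ICC.** None is given, and for a difference-in-differences the relevant one is that of BMI change, after stable school differences are removed. It may be small. This stands. But under school-level arms the 6-df result is below 80% even at zero.
- **The SD.** A reader might infer that 0.96 is simply wrong. The documents do not support that. It may be an SD of change, which is the scale the planned estimate uses, and the source it came from is not available here. The required correlation of about 0.96 is plausible for BMI, and nothing in the article contradicts it. The implied SD of 3.2 to 3.6 joins two populations, neither of which is the trial's. Nor should the power of an end-line-only BMI comparison be held against the plan, because that is not its effect estimate.
- **The headline.** A reader might infer that 80% power is definitely not delivered. That goes too far: the shortfall depends on an ICC and a unit of allocation that the article does not fix.

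**Conclusion.** The concern holds as a fault in the design assumptions. The stated power rests on independence between teachers, which the protocol's own definition of clusters and its group delivery contradict.

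With SD 0.96, a difference of 0.5 and 58 analysed per arm, the size is conditional. School-level arms give about 75/70/58/45% at ICC 0.01/0.02/0.05/0.10 by the normal approximation, or about 60/55/44/34% on 6 degrees of freedom. Individual allocation gives about 77–79%, 68–74% and 58–69% at ICC 0.01, 0.05 and 0.10. All ICCs and session-group sizes are assumptions.

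On the inputs, the supportable statement is narrower: 0.5 must be a raw difference, and 0.96 is unlabelled and not credible as a between-woman SD of BMI, but usable if it is an SD of change.

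**What to change.** 1. Reconcile the control-group paragraph of section 2.2.2 with section 2.7.2, and state whether schools or teachers are allotted to arms.
2. In section 2.8, label 0.96 as the SD of BMI change, or replace it with a figure that is, and label 0.5 as a difference in kg/m².
3. Apply a design effect that matches the allocation over a stated ICC range for BMI change, such as 0.01 to 0.10. If by school, use 1 + (m − 1) × ICC with degrees of freedom for 8 schools. If by teacher, allow for clustering by session group in the intervention arm.
4. Replace 80% with the resulting power, or with the difference detectable at 80% power with 130 teachers in 8 schools. Under school-level allocation that is about 0.64 to 0.92 kg/m² for ICC 0.01 to 0.10.

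The cost is protocol wording and a less favourable power statement. No extra enrolment is required.
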